# Intelligent rehabilitation assistant system to promote the early functional recovery of the elderly patients with femoral neck fracture after hemiarthroplasty (HA)

**DOI:** 10.1097/MD.0000000000023078

**Published:** 2020-11-13

**Keywords:** electronic information technology, hip fractures, opening and double-dummy RCT, rehabilitation

## Abstract

**Background::**

Femoral neck fracture is a common type of hip fracture, which has a high morbidity and mortality. Surgical treatment is the first choice. However, the functional rehabilitation after operation has not been paid enough attention. In addition, the quality of exercise is difficult to quantify, and the rehabilitation is lack of standards. Therefore, the intelligent rehabilitation assistant system which could record exercise details, might be used to evaluate the quality and adherence to the prescribed exercise to this fragile group of patients has great relevance, so as to provide new ideas for postoperative rehabilitation of hip fracture.

**Methods::**

This is an opening, prospective, double-dummy RCT. Fifty femoral neck fractures patients, older than 65 years and are about to hospitalize for HA, will be invited to study. The sample will be divided into monitoring group and control group randomly at a 1:1 ratio. The prescribed exercises need to be done continuously for 2 weeks. The monitoring group needs additional use intelligent rehabilitation assistant system. Each subject will receive a total of 4 follow-up visits at the designated time (2 weeks, 4 weeks, 12 weeks, and 24 weeks). The following factors will be talked as dependent variables:

Each subject will receive a total of 4 follow-up visits at the designated time, and the findings will be analyzed statistically considering a 5% significance level (*P* < .05).

**Discussion::**

Exercise under monitor may improve patients compliance and exercise quality, and accelerate the rehabilitation process. This protocol reported in accordance with the CONSORT 2010 checklist and SPIRIT 2013 Checklist.

**Trial registration::**

The trial is registered at Chinese Clinical Trials Registry (ChiCTR2000033213, May 24, 2020).

## Introduction

1

Femoral neck fractures are subset hip fractures, which accounts for about 3% of whole-body fracture and more than 40% of hip fracture.^[1]^ Hip fractures, considered the most serious results of falls or osteoporosis, usually confirmed in trauma patients with the symptom of hip pain. Every year approximately 1.6 million people over the world sustain hip fractures. In general, the dominant cause of hip fractures is low-energy injuries, and it affected men and women equally.^[2]^ The hip fractures always lead to hospitalization, because of its severity.

A study found that hip fractures take at least 2.35 million disability-adjusted lives each year, and more than 5 million people all over the world experience disability.^[3]^ A displaced femoral neck fracture is a severe injury for all ages. In most cases, it requires surgery. Even if it is not a displaced femoral, the situation is also not optimistic. A systematic review shows that the union rate of patients is 92.6%, the avascular necrosis rate is 7.7% after surgery. For those patients who treated conservatively, the union rate and the avascular necrosis rate is 68.8% and 10.3%.^[4]^ There are many options for the treatment, including internal fixation, hemiarthroplasty (HA), and total hip arthroplasty (THA). HA can help ambulation and function recovery, for the surgeons, it is becoming more likely to be chosen.^[5]^ However, even with the scheduled surgery, the patients still in the risks of subsequent surgical complications, reduced function, hip pain, and reduced health-related quality of life.^[6]^ To reduce the morbidity and mortality caused by hip fracture, not only the treatment for the broken bones but also the treatment for the general weakness is needed.^[7]^

Since the risks of femoral neck fracture increasing exponentially with the age of the patients and the trend of population aging, criteria for treatment measure is needed to ensure the optimal outcomes.^[4]^ The hip fracture patients might be unable to regain independence because of the serious edema of the lower extremity and the reduced knee-extension strength,^[8]^ especially after surgery. Comprehensive rehabilitation could improve mobility, balance, and self-reported activities of daily living. Recently, an increasing number of studies are devoted to lower-limb progressive resistance exercise and balance training to improve several functional outcomes,^[7,9–13]^ such as sitting knee extension and for leg press exercise,^[12]^ strengthening exercises for the hip extensors and abductors, knee extensors,^[10]^ standing- walking practice with eyes closed,^[14]^ etc.

However, as reported, in long-term follow-up studies, conventional rehabilitation programs had no significant effect on falling again or reducing mortality.^[15–17]^ As the matter of fact, with a different understanding of doctors advice, and different health states after a hip fracture, it is inappropriate to confirm the above conclusions from existing analysis under the situation with the ignorance of fulfilling the quality of rehabilitation programs. For example, The Study of Hall WJ^[18]^ arranged 20 minutes -daily training in the morning and evening during the hospitalization for the intervention group, the specific plan included balance, walking exercises, flexion of lower limb joint and individualized progressive resistance. The study showed that although these targeted training could not shorten the length of hospital stay, improve sudden delirium, or reduce the re-entry rate of 90 days, but there was statistically significant benefit soverusual both in the Barthel Index and the SPPB scores.

Therefore, accurately describing the pace of recovery is crucial, which has important use to inform clinical decision-makers and caregivers and patients.^[19]^

In addition, in recent years, more and more researchers have used applications to help guide postoperative rehabilitation of orthopedic diseases, and have achieved good results. For example, Hardt S used an app-based active muscle training program for patients after total knee arthroplasty (TKA) to assess whether the scheduled physical training would improve the outcomes of the immediate postoperative period after lower limb surgery. Throughout their hospital stay, each person of the training group was permanently provided with a prototype of the knee trainer and smart tablet with Genu Sport application for the active knee extension training program, the result shows that this intelligent program could improve the outcome after TKA in the immediate postoperative period, particularly in reducing the pain and improving the range of joint ROM.^[20]^ Although we all acknowledge the above consensus, there are still many difficulties to ensure the patients received an integrated unit with shared care due to the different medical policies and medical forces of various countries.

In this study, the intelligent rehabilitation assistant system was used to record exercise details and assess the quality of rehabilitation. Objective to evaluate the quality and adherence to the prescribed exercise to this fragile group of patients. So that we can continuously monitor the limb movement and better observe the outcome of comprehensive rehabilitation after hip fracture operation. The research hypothesis: regular and quality rehabilitation exercise could improve the limb function and accelerate rehabilitation. This is a new exploration, patient-centered interdisciplinary care of hip fractures, interdisciplinary teamwork involved orthopedic surgery, rehabilitation department, geriatric medicine, anesthesiology, nursing, etc.^[21–23]^

## Methods/design

2

### Study design and setting

2.1

This is an opening, prospective, double-dummy RCT. There are 50 patients in total with femoral neck fracture will be recruited from the First Affiliated Hospital of Guangzhou University of TCM, Guangzhou, China. The flow chart and study period are shown respectively in Figure 1. After obtaining written informed consent, the eligible participants will get complete examination before surgery as well as hemiarthroplasty, and then they will be randomly assigned to a monitoring group or a control group in a 1:1 ratio.

**Figure 1 F1:**
[figure not shown]
Research flow chart.

### Participants

2.2

Participants will be recruited via inpatients of a standard-compliant femoral neck fracture, which had a clear history of trauma, hip or greater trochanteric pain, aggravating during activity and was forced to bend the hip and knee, the deformity of pronation and adduction was common. Participants should meet the X-Ray and CT images of a femoral neck fracture. The information about the study, the use of the monitor, and the schedule will be carefully explained before enrollment.

### Eligibility criteria

2.3

#### Inclusion criteria

2.3.1

In accordance with the patients with femoral neck fracture were admitted to the hospital from November 2021 to January 2022. The time from this injury to the hospital was no more than 3 weeks.

Age ≥65.The cause of injury is low energy injury.After the relevant examination is completed in a hospital, it is judged to be suitable for hemiarthroplasty (the implant materials is a ceramic hip prosthesis, offered by Belang Medical (Shanghai) International Trade Co., Ltd). The operation was performed by the same group of doctors, with more than 5 years working experience, and be able to complete the operation skillfullyHave certain activity ability before this injury, and can take care of them to some extent.According to the X-ray examination, the bone condition of the patients belongs to Singh grade 4 to 6.^[24]^

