#### The primary outcome

2.7.1

The primary outcome is a change in the Harris Hip Score (HHS). HHS is used most commonly as a postoperative functional evaluation tool for hip fractures. The following 7 symptoms can be evaluated by HHS: the degree of the pain, the daily activity function, gait, walking aids, walking distance, deformity degree, and activity scope. The score is judged and recorded by researchers with a totally 100 (excellent: 90∼100, fine: 80∼89, secondary: 70∼79, and not satisfactory: <70), the higher scores indicating better joint function.

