#### The secondary outcome

2.7.2

The Secondary outcome measures are as follows:

Activity of Daily Living (ADL): it refers to the necessary activities that a person carries out every day to meet the needs of daily life, including eating, dressing, washing, bathing, toileting, dressing, etc. Functional movement includes turning over, sitting up from bed, transferring, walking, driving a wheelchair, going up and downstairs, etc. The total score is 100 (100 points: life self-care; 60 points and above: basic self-care; 40 to 60 points: life needs assistance; 20 to 40 points: life needs great assistance; less than 20 points: life completely dependence.)The timed “up & go” text: a fast and quantitative evaluation method of functional walking ability only needs a chair and a stopwatch. During the assessment, the patient is sitting on the chair with the back of the chair and hands on the armrest. If the walking aid is helpful, the walking aid is held in the hand. The reference object set 3 meters away from the seat. With the tester sends out the command of “start”, the patient stands up and walks to the reference point and returns. There is none physical help during the test. The tester records the time taken (in seconds) and the risk of falling during the completion of the test. Before the formal test, the patient is allowed to practice 1 to 2 times to ensure that the patient understands the whole test process. Researchers need to record the complete time of the experiment and evaluate the risk of completing the action. (1 point: normal. 2 points: very slight abnormality. 3 points: slight abnormality. 4 points: moderate abnormality. 5 points: severe abnormality.)Visual analog scale (VAS): The subjects participating in the study will indicate the intensity of their pain using a VAS of 100 mm. They must signal on a horizontal line of 100 mm where they would place their pain, where 0 mm indicated “no pain” and 100 mm would be “the worst pain imaginable”.Postoperative complications: Such as pulmonary embolism, lower extremity deep vein thrombosis, loosening, and displacement of the prosthesis, periprosthetic fracture, postoperative infection, etc.6-month mortality after HA:

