### Sample size calculation

2.9

The sample size is calculated by using the software PASS 2011. Based on the analysis of the variance of means, and estimating an alpha risk of 5% (0.05), a beta risk of 10% (0.10), a unilateral contrast, a typical deviation of 10% (0.10). The primary outcome is the HHS, according to Wang j et al,^[25]^ 6 months after HA, the mean value of Harris score was 86.580 and the standard deviation was 4.629. The experimental assumed the mean value of the monitoring group is 92.650 and the standard deviation is 3.664, and a rate of follow-up losses of 20%, 11 subjects are required in each group, combined with the actual situation of patients in the hospital. Finally, we will include 50 patients divided into 2 groups, each group contains 25 subjects, to overcome this value to assume the possible loss of follow-up, the calculation results are shown in Figure 6.

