### Data management and statistical analysis

2.10

Data are collected from electronic medical records at the study sites, participants study-specific diaries. All collected data for the trial is entered electronically in the encrypted database built by the researchers ourselves which could not be accessed by a third party. The system sets a fixed personal account according to the users organization and role. All attempts to log in to the system will be recorded. All data changes are recorded by user and time, so it can be tracked. All the research data were collected in the First Affiliated Hospital of Guangzhou University of Traditional Chinese Medicine, part of which was recorded in the orthopedic ward and some in the outpatient department. The data management system will check whether all the input data are of correct type, for example, the date must be valid date, and the number must be valid number, at the same time, logical check/verification is designed. Composition of data monitoring committee (DMC) will be undertaken by the Ethics Committee of the First Affiliated Hospital of Guangzhou University of Traditional Chinese Medicine and responsible for reviewing data security once a year.

The statistical analysis will be carried out by IBMSPSS Statistics 21 software. Demographic and baseline data will be summarised using descriptive statistics and graphs as appropriate. Continuous variables will be summarised by descriptive statistics. Categorical variables will be summarised in frequency tables. For the contrast of intragroup hypotheses, Student *t-*test for paired variables will be applied in the case of parametric distribution and Kruskal–Wallis H for nonparametric distributions. Kolmogorov Smirnov test will be used to test the normality of variables. One-factor analysis of variance (ANOVA) will be used in the case of parametric distributions and Kruskal–Wallis H for non-parametric distributions. Statistical tests used to compare between treatments groups will be done two-sided at a signifi-cance level of 5%. The confidence level used will be 95% (0.05), and the power of the study will be 90% (0.1).

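### Self-care before the injury is recorded and should predict the hip score, yet the group comparison is fixed as an unadjusted one-factor test

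*Protocol article*

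**What the plan says.** - **Entry (section 2.3.1).** Age 65 or older with no upper limit, low-energy injury, judged suitable for hemiarthroplasty, Singh grade 4 to 6, and "certain activity ability before this injury, and can take care of them to some extent". Singh grade concerns bone and suitability is a surgical judgement, so the quoted phrase is the only functional criterion. Section 2.3.2 excludes no one for walking ability or dependence.
- **Primary outcome (section 2.7.1).** Change in HHS. Among its seven components are "the daily activity function, gait, walking aids, walking distance".
- **ADL scale (section 2.7.2).** Its bands include "60 points and above: basic self-care; 40 to 60 points: life needs assistance; 20 to 40 points: life needs great assistance".
- **Baseline data (end of section 2.7).** Self-care before the injury is among the items taken from the medical record.
- **Planning values (section 2.9).** For controls, "6 months after HA, the mean value of Harris score was 86.580 and the standard deviation was 4.629". For the monitoring group, an assumed mean of 92.650 and SD of 3.664. Eleven per group are required and 25 per group will be enrolled, with 20% loss expected.
- **Analysis (section 2.10).** Paired t-tests are assigned to within-group contrasts. One-factor ANOVA, or Kruskal–Wallis for non-normal data, is the method left for comparing groups. "Statistical tests used to compare between treatments groups will be done two-sided" at 5%. No covariate is named.

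**The concern.** The entry wording lets in patients who managed fully before the fracture and patients who needed help. On its face, someone in the 40 to 60 ADL band takes care of himself to some extent and qualifies. Walking aids, walking distance and daily activity all count towards HHS, so part of the spread in 24-week HHS would be expected to come from function before the fracture and not from the allocated intervention.

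A one-factor test puts all of that spread into the error term. It also leaves in the estimate any chance difference between arms in prior function. The randomization section describes no stratification that would limit such a difference. At stake are the precision and credibility of the primary comparison in a trial of 50 patients. The variable that would deal with both problems is already being collected.

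**Working it through.** **Inputs from section 2.9.** Difference 92.650 − 86.580 = 6.07. Pooled variance (4.629² + 3.664²)/2 = 17.43, so SD 4.17 and standardised difference 6.07/4.17 = 1.45.

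**The plan's own figure.** A two-sided 5% t-test with 11 per group has power 0.900. A one-sided test needs 9, and 9 × 1.2 = 10.8, rounded to 11. The stated 11 reproduces by either route. The two-sided test is used below because section 2.10 specifies it. Section 2.9 states "a unilateral contrast", and that conflict is a separate matter.

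**What the planning values imply.** Taken as normal, 92% of controls score 80 or more and 77% of the monitoring group score 90 or more. The calculation thus assumes a narrow spread around high scores.

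**Slack from enrolling 25.** After 20% loss, 25 × 0.8 = 20 per arm. With SD 4.17, power is 99%. Power stays at 90% up to an SD of 5.8 and at 80% up to 6.7.

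**Effect of mixed prior function (assumed values).** Let a share f of patients score g points lower, with the same treatment benefit for all.

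- Unadjusted variance: V = 17.43 + f(1 − f)g².
- Variance if the covariate captures half of the added part: V½ = 17.43 + ½ f(1 − f)g².
- Power from the noncentral t with noncentrality 6.07/(√V × √(2/20)), on 38 degrees of freedom unadjusted and 37 with the covariate.

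| f, g | f(1 − f)g² | SD unadjusted | Power | SD adjusted | Power |
|---|---|---|---|---|---|
| 10%, 10 | 9 | 5.14 | 95% | 4.68 | 98% |
| 20%, 10 | 16 | 5.78 | 90% | 5.04 | 96% |
| 20%, 15 | 36 | 7.31 | 73% | 5.95 | 88% |
| 30%, 20 | 84 | 10.07 | 46% | 7.71 | 68% |

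**Chance imbalance.** At 25 per arm, each extra lower-functioning patient in one arm moves the group difference by g/25. The probabilities come from two independent binomial counts, in either direction.

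- f = 20%, g = 15 (0.6 points per patient): a shift of at least 6.07 needs 11 patients, probability 0.02%. A shift of at least 3 needs 5 patients, probability 11%.
- f = 30%, g = 20 (0.8 points per patient): a shift of at least 6.07 needs 8 patients, probability 2.0%. A shift of at least 3 needs 4 patients, probability 28%.

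**The case against.** **The source study may have been just as broad.** Its entry criteria are not given. If it admitted the same mix, its SD already contains this spread and the formula above counts it twice. This stands. The power figures are conditional, and the protocol does not show that the variance will exceed the planning value.

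**Nothing shows that dependent patients cannot reach the planned scores.** A reader might infer this from the HHS components. The protocol gives no weights for them and no HHS for patients with limited prior function. It supports only that such patients would be expected to score lower.

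**Imbalance could swamp the effect.** A reader might infer that with 25 per arm it could create or hide the full 6 points. The probabilities above do not support that. Shifts of about half the effect are possible only under the larger assumed deficits.

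**Enrolment is already generous.** True. Going from 11 to 25 per group absorbs an SD up to about 5.8 at the planned power, and section 4 allows for a later recalculation. This covers the milder scenarios but not the two larger ones.

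**A broad criterion suits the aim.** The protocol describes its patients as a fragile group. Narrowing entry would cost recruitment and generalisability, and an ADL cut-off of 60 would not necessarily exclude people who use walking aids. This stands, so tighter eligibility is not part of this point.

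**Covariates belong in an analysis plan.** Their coding may. But section 2.10 does not leave the method open: it names a one-factor comparison, and that is what this point addresses.

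**Analysing change already adjusts.** The pre-evaluation takes place after the fracture, so subtracting it would not be expected to remove differences in function before the injury.

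**Conclusion.** The point holds as one about the analysis. The plan admits patients of varied prior function, uses an outcome that such function would be expected to predict, records the predictor, and then fixes a comparison that ignores it. Adjustment would be an improvement at almost no cost.

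The size of the gain is not known. Under the assumed shares and deficits, and with the source SD assumed free of this mix, it runs from about 3 percentage points of power (95% to 98%) to about 22 (46% to 68%). The assumption that the covariate captures half of the added variance is also not from the protocol.

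A reader might go further and conclude that the trial is underpowered or that the entry criterion is wrong. The protocol supports neither. Both need the share of dependent patients, their HHS and the source study's criteria, none of which it gives.

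**What to change.** In section 2.10, make the primary between-group comparison an ANCOVA, or equivalently a linear model, of HHS at 24 weeks on group, with self-care before the injury as a pre-specified covariate. Report the adjusted difference with its two-sided 95% confidence interval. Fix in advance how the covariate is recorded. The protocol's own ADL score, taken by history for the period before the fracture and before allocation, would serve. The unadjusted one-factor comparison can stay as a supporting analysis.

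**Cost.** One residual degree of freedom (38 to 37 with 20 completers per arm) and a defined scale for an item already collected. Eligibility, recruitment and sample size do not change. A threshold on ADL before the injury remains an optional design choice for the investigators, since it would narrow who can enter and to whom the result applies.
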